#### Interim analyses {21b}

No formal interim analysis is planned.

#### Methods for additional analyses (e.g. subgroup analyses) {20b}

Whether there is a differential intervention effect over the socio-economic gradient will be explored. The dependent variable of this analysis will be defined in the same way as was defined for primary and secondary outcomes. This outcome will be analysed in the same way as other outcomes; however, the estimated treatment effect and corresponding 95% CI will be reported (instead of a 97.5% CI) along with the *p*-value. However, the logistic regression model will include IMD, and an interaction between IMD and intervention and an interaction between IMD and site. Other socio-economic factors such as employment status may also be considered, as well as gender and ethnicity, while acknowledging the potential for multicollinearity.

A further analysis of the primary outcome (using logistic regression) will also adjust for the following baseline covariates:Education level (‘No formal qualifications’ will be the reference category)Index of multiple deprivation (IMD)Modified dental anxiety scale (MDAS)

The baseline covariates of education and IMD will be assessed for multicollinearity as they may be correlated. If it is found that there is an association between them, then one of them will be removed.

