#### Secondary objectives

To identify whether the behavioural intervention has different effects across the socio-economic gradient.To identify the psychological factors which mediate any intervention effect.To identify whether there is a difference between intervention and control groups in self-reported rates of attendance and/or attempts to make an appointment at a dental practice for planned dental care during the follow-up period.To identify whether there is a difference between intervention and control groups in rates of attendance at a dental practice (as measured by BSA data) for a planned care appointment within 18 months.To identify whether there is a difference between intervention and control groups in oral health quality of life at 6 and 18 months.To identify whether there is a difference between intervention and control groups in halitosis and bad taste as indicators of dental infection at 6, 12 and 18 months.To identify whether there is a difference between intervention and control groups in clinical dental treatment received at 6, 12 and 18 months.To identify whether there is a difference between intervention and control groups in self-reported rates of attendance for urgent dental care at A&E, GP practices and urgent dental care services at 6, 12 and 18 months.To identify whether there is a difference between intervention and control groups in rates of antibiotics or analgesics for dental problems prescribed by a dentist, GP Accident and Emergency department or walk-in centre at 6, 12 and 18 months.To monitor any change in dental anxiety after receiving the intervention.To estimate the cost effectiveness of the intervention compared with usual care at 12 and 18 months.

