### Statistical methods

#### Statistical methods for primary and secondary outcomes {20a}

An extract of the NHS BSA data will be obtained after 12 months (52 weeks) of recruitment. This will aid in the preparation of analysis code before receiving the 18-month (78 weeks) data. Final analysis of the first primary outcome will be conducted on the 18-month data. Analysis of the first primary outcome will involve the number and percentage of participants found to have a planned dental appointment within 12 months which will be reported for each treatment group separately. The denominator will be the number of randomised participants in each treatment group. A comparison between groups will be done using logistic regression, adjusted for the stratification factor site as a random effect (random intercept only). The derived binary variable for attendance for a planned appointment within 12 months will be the dependent variable. The odds ratio and corresponding 97.5% confidence interval will be reported and *p*-value. A sensitivity analysis will be conducted removing all participants from the above primary analysis who were recruited in dental practices (i.e. not randomised at the Dental Hospital) and who do not have a matched NHS BSA record at baseline. This is to assess the impact of including the participants who were not successfully matched in the NHS BSA data at baseline which may indicate that it was possible to get NHS BSA data at later timepoints.

Analysis of the second primary outcome will involve summaries of OHIP-14 scores presented at baseline and 12 months separated by treatment group, for all participants included in this analysis. The OHIP-14 scores at 12 months will be analysed using linear regression, adjusting for the baseline value of OHIP-14 and the stratification factor site as a random effect (random intercept only). The estimated treatment effect and corresponding 97.5% CI will be reported along with the *p*-value. This will be a complete case analysis, only participants with valid baseline and 12-month questionnaires will be included in the analysis.

A second analysis will also adjust for other pre-specified baseline variables, including dental anxiety and socio-economic status.

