## Discussion

This trial is at the pragmatic end of the spectrum of clinical trial design, with its purpose focused on evaluating the effectiveness of the intervention under the usual condition in which it might be applied, whilst maintaining internal validity [44]. This presents particular challenges to its implementation since dental practice activity sits within an independent contractor model with dental staff remunerated according to Units of Dental Activity undertaken. Dental practitioners are known to perceive financial rewards for being involved in research as relatively unattractive, while also feeling they have relatively little knowledge and skills in the area [45]. Integration of trial processes within routine workloads is a key lesson from previous trials situated in dental practice, and hence a flexibility was built into the study flow diagram so that trial processes and delivery of the intervention could be undertaken at any time during the urgent dental care appointment [46].

Previous trials in dental practice have found significant differences in intervention effects between dental practices [47] and so it will be important to examine differences by site type (dental practice [delivering in-hours urgent care and out of hours care], Dental Hospital), as well as incorporating measures to ensure and monitor fidelity of intervention delivery. The RETURN trial will be supported by embedded qualitative work to support understanding the contextual issues influencing the implementation of the intervention, and the trial itself.

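### The socio-economic gradient analysis names the treatment coefficient, not the IMD-by-intervention interaction, as its result, and the rule for removing education or IMD leaves the adjusted model dependent on the data

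*Protocol article*

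**What the plan says.** The Secondary objectives of the protocol article include: "To identify whether the behavioural intervention has different effects across the socio-economic gradient". The section on additional analyses {20b} takes this up: "Whether there is a differential intervention effect over the socio-economic gradient will be explored". It then says that "the estimated treatment effect and corresponding 95% CI will be reported (instead of a 97.5% CI", together with the p-value, and that "the logistic regression model will include IMD, and an interaction between IMD and intervention and an interaction between IMD and site". It gives no scale or centring for IMD and does not name the interaction estimate as an output.

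The same section describes a second model: "A further analysis of the primary outcome (using logistic regression) will also adjust for the following baseline covariates". The covariates are education level, IMD and the dental anxiety score. Education and IMD are to be checked for multicollinearity, and: "If it is found that there is an association between them, then one of them will be removed". The section gives no threshold and does not say which of the two is removed. The section on statistical methods for primary and secondary outcomes {20a} describes its covariate-adjusted second analysis as using baseline variables fixed in advance.

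**The concern.** Whether the effect differs by deprivation is part of the trial's overall objective. The quantity that answers it is the interaction between IMD and intervention. Once that term is in the model, the coefficient labelled treatment is the effect at one value of IMD, set by the coding. It is in general neither the average effect nor the difference in effect along the gradient. If it were printed as the result, a reader could take an imprecise estimate at IMD = 0 as absence of benefit, or as a contradiction of the primary result, and would still not know whether the gradient matters.

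The removal rule raises a smaller matter. An adjusted analysis is credible because its covariates are fixed before the data are seen. Here the set depends on an observed association, and the choice of which variable to drop is left open.

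**Working it through.** The additional-analyses section states no figure of its own. The only trial figure needed is N = 1180 at 1:1 (Sample size and Trial design sections). It is based on 559 per group, which reproduces exactly for 31% against 40% at two-sided alpha 0.025, 80% power and continuity correction (552 for 30% against 39%). Nothing below changes it.

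**1. What the treatment coefficient means.** Write the model, leaving site aside, as

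logit P(attend) = a + b·T + c·IMD + d·T·IMD.

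The log odds ratio for treatment at a given IMD is b + d·IMD. So b is the effect at IMD = 0, and d is the change in effect per unit of IMD. If IMD is shifted or reversed, b changes; d keeps its size and only its sign can flip.

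Illustration. These inputs are assumptions except where noted:
- N = 1180, 1:1 (from the protocol).
- Log odds ratio 0.400 at decile 3.5, from 30% against 39%: (0.39/0.61)/(0.30/0.70) = 1.49. These rates are the protocol's control rate and its 9-point difference.
- IMD in deciles, skewed to deprivation, mean 3.43.
- IMD main effect 0.05 and interaction 0.08 log-odds per decile.
- No site effect; 400 simulated trials.

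Expected treatment coefficients by direct substitution:
- raw deciles (IMD = 0): 0.400 + 0.08 × (0 − 3.5) = 0.120, odds ratio 1.13;
- centred (decile 3.43): 0.400 + 0.08 × (3.43 − 3.5) = 0.394, odds ratio 1.48;
- reversed as 11 − decile (zero at decile 11): 0.400 + 0.08 × (11 − 3.5) = 1.000, odds ratio 2.72.

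Simulated results:

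| Coding of IMD | Treatment odds ratio | SE (log scale) | Runs with p < 0.05 | Interaction, absolute size (SE) | Interaction, runs with p < 0.05 |
|---|---|---|---|---|---|
| Raw deciles | 1.13 | 0.208 | 10% | 0.083 (0.047) | 43% |
| Centred | 1.50 | 0.125 | 92% | 0.083 (0.047) | 43% |
| Reversed deciles | 2.80 | 0.372 | 78% | 0.083 (0.047) | 43% |

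Raw and reversed deciles put zero outside the observed range of 1 to 10, so those two coefficients describe no participant. The interaction does not depend on the coding. Its average corresponds to a ratio of odds ratios of exp(0.083) = 1.09 per decile, with an approximate 95% CI of exp(0.083 ± 1.96 × 0.047) = 0.99 to 1.19. That is the form of result the objective calls for.

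**2. The removal rule.** Variance inflation of each covariate from a correlation r between the two is 1/(1 − r²):
- r = 0.057: 1.003
- r = 0.10: 1.01
- r = 0.20: 1.04
- r = 0.30: 1.10
- r = 0.50: 1.33

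This inflation falls on the coefficients of education and IMD. Treatment is randomised, so it is close to uncorrelated with both, and its precision is barely touched.

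How often the rule would act depends on the meaning of association, which the article does not define. Suppose, as an assumption, that it means a 5% test of a correlation. The smallest significant value at N = 1180 is about 1.96/√1180 = 0.057. For a true r of 0.10, the probability of removal is Φ(atanh(0.10) × √1177 − 1.96) = Φ(3.44 − 1.96) = 0.93. A covariate would then be removed when the variance inflation is only 1.01.

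**The case against.** The strongest reply on the gradient model is that the quoted sentence mainly sets the confidence level, 95% in place of 97.5%, and that the interaction follows in the next sentence. A full analysis plan exists and may give the IMD scale, the centring and the display of the interaction. This stands in part. A reader might infer that the model cannot answer its question, and that would be wrong: the term that answers it is in the model. What remains is that the article states an output, and the output it states is not that term.

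On the removal rule, the reply is that association can be read as the result of the multicollinearity check in the sentence before. Under a variance-inflation criterion the rule might rarely act. Education is also categorical, so a single correlation fits it only loosely. This stands against any claim that the rule would almost always fire; the 93% holds only under the stated assumption. It does not settle which covariate goes. Nor does it supply a reason to remove either one when the target is a randomised treatment effect.

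A reader might also infer that the IMD-by-site term is an error, or that it stands in for a missing intervention-by-site analysis. The documents do not support either. How that term fits with a model "adjusted for the stratification factor site as a random effect (random intercept only" is not spelled out, but nothing shows that it harms the interaction of interest. The gradient question does not need an intervention-by-site term. The Discussion says that "it will be important to examine differences by site type", but that is a separate interest and its method may sit in the analysis plan.

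**Conclusion.** The point holds in two limited parts. First, the reported quantity named for the gradient analysis depends on an unstated coding of IMD and does not measure the differential effect. This follows from the form of the model and needs no numerical assumption; the odds ratios of 1.13, 1.50 and 2.80 only illustrate it under assumed deciles and an assumed interaction. With centred IMD the coefficient would be a sensible effect near the average, but it still would not address the gradient.

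Second, the removal rule makes the adjusted model data-dependent for practically no gain. It would be too strong to say that the adjusted model becomes invalid, because a randomised comparison remains valid after a baseline covariate is dropped.

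Both parts concern secondary or exploratory analyses. The primary analyses, the alpha split and the sample size are untouched. The changes should be made, but nothing in the trial's main conclusions depends on them.

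**What to change.** In the additional-analyses section, and in the analysis plan if it reads the same way:

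- Name the IMD-by-intervention estimate as the result of the gradient analysis: for attendance, the ratio of odds ratios per stated unit of IMD, with 95% CI and p-value.
- Add treatment effects with 95% CIs at stated IMD levels from the same model, and state the scale and direction of IMD and that it is centred.
- Keep both education and IMD in the adjusted model and delete the removal rule.

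The cost is a few sentences of wording. No new data, participants or follow-up are needed.

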## Introduction

### Background and rationale {6a}

Dental diseases are both very common and expensive to treat, with costs amounting to an estimated $356.80 billion in treatment expenditures and $187.61 billion in productivity losses worldwide [1]. Unfortunately, an inverse care law exists whereby those who have the highest dental needs are the least likely to receive good quality care—a pattern which is both considerable and globally consistent [2, 3]. A social patterning of dental attendance exists where those from more deprived socio-economic backgrounds are less likely to visit a dentist for planned visits [3–5], even though poorer oral health disproportionately affects those at the lower end of the socio-economic spectrum [6–8]. Several studies have shown that socio-economic inequalities in oral health are, at least some extent, mediated by dental attendance [9–11]. A large body of evidence, including longitudinal studies, show that dental attendance is linked to better oral health [4, 12, 13]. Patients who are regular dental attenders are also more likely to report fewer negative impacts of poor oral health on their quality of life [5].

As many as a third of the UK population report that they only attend a dentist when they have a problem, or never do [14]. While early studies tend to adopt a dichotomous distinction between regular and irregular attenders [6], often based on dental attendance over the preceding 12 months, more recent studies have started to look at patterns in dental attendance in terms of the lifecourse [5, 15–17]. These studies show that only a minority of patients maintain dental attendance patterns consistently throughout their lives, and a small minority never visit a dentist. Consistent planned dental visits over the long term have been shown to be associated with better oral health, compared to patients who do not visit a dentist at present, but used to do so, or patients who have never regularly attended dental care services [5, 15, 17].

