### Trial design {8}

The RETURN trial is a randomised, open-label, superiority study involving delivery of an opportunistic psychological intervention to urgent dental care users developed to increase the uptake of planned dental care and reduce health inequalities. The allocation ratio between intervention and control is 1:1. The trial will recruit 1180 urgent dental care users over 12 months. Participants will be followed up at 6, 12 and 18 months after randomisation.

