### Data collection and management

#### Plans for assessment and collection of outcomes {18a}

Table 1 provides a summary of procedures and assessments relative to participant timelines. Patients receiving dental care in an NHS dental practice following baseline will have a centrally held record in data held by NHS BSA, which will require participant IDs collected at baseline to be matched with participant NHS BSA identifiers. To maximise matching of participant descriptors with routinely held NHS BSA follow-up data, participant postcodes will be checked at each follow-up point in case this has changed since baseline. For participants receiving dental care in the Dental Hospital (DH) following their baseline data, details will be retrieved from clinical records held in the Dental Hospital identified by their unique RQ number. This follow-up data will be collected using a CRF proforma and conducted as an audit of participant DH records. Follow-up data collected by telephone calls by the central research team will be audiotaped and 10% checked by a different researcher than the researcher entering the data during the telephone call. Where disagreements are identified, these will be addressed and resolved by agreement, and any data entry errors rectified. Data collection forms can be obtained from the research team.

**Table 1 Tab1:** Schedule of processes and assessments

Procedures		Screening /Baseline	RETURN Intervention Group	Control Group	Follow-up		
					6 months (+/− 4 weeks)	12 months (+/− 4 weeks)	18 months (+/− 4 weeks)
Assessment of Eligibility Criteria		X					
Signed consent form		X					
Urgent dental treatment (trial processes and intervention around delivery of urgent care)		(X)	(X)	(X)			
Collection of Contact Details, including Home Postcode (to determine IMD as a mediator)		X					
Verification of NHS BSA Matching Descriptors					X^d^	X^d^	X^d^
Collection of RQ6 number^a^		X					
***Self-Reported Assessments***	Socio-economic status (Education level, employment and benefit status)	X			X^b^	X^b^	X^b^
	Age	X					
	Gender (including ‘prefer not to say’)	X					
	Ethnicity	X					
	OHIP-14	X			X	X	X
	Halitosis and Bad Taste	X			X	X	X
	EQ-5D-5L questionnaire	X			X	X	X
	Protection motivation theory questionnaire	X	X^c^	X^c^	X	X	
	Modified dental anxiety scale (MDAS)	X			X	X	X
	Use of Routine Dental Practices and Type (NHS or Private)	X			X	X	X
	Use of Student Teaching Pathway (Dental Hospitals)	X			X	X	X

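### For attendance, the deprivation gradient is tested on the odds-ratio scale, where a null interaction can go with a modest widening of the absolute gap; risk differences by IMD should be reported alongside it

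*Protocol article*

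**What the plan says.** All references are to the protocol article.

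- Trial design {8} describes the intervention as "developed to increase the uptake of planned dental care and reduce health inequalities".
- Secondary objectives include: "To identify whether the behavioural intervention has different effects across the socio-economic gradient". No scale is named. Objectives {7} and section {20b} both present this as exploration.
- Section {20b} specifies the model for attendance: "However, the logistic regression model will include IMD, and an interaction between IMD and intervention". An IMD-by-site interaction is added as well. On reporting it says: "the estimated treatment effect and corresponding 95% CI will be reported (instead of a 97.5% CI").
- Section {20a} gives the effect measure for attendance: "The odds ratio and corresponding 97.5% confidence interval will be reported". Attendance percentages are described by treatment group, not by IMD.
- Sample size {14} expresses the worthwhile effect in absolute terms: 30% rising to 40%, reduced to a 9-point difference to allow for contamination.
- Background {6a} says that "those from more deprived socio-economic backgrounds are less likely to visit a dentist for planned visits".
- Table 1, under section {18a}, lists "Home Postcode (to determine IMD as a mediator").

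**The concern.** A product term in a logistic model asks whether the intervention multiplies the odds of attendance by the same factor at every level of deprivation. Whether the percentage-point gap between more and less deprived patients shrinks, stays or grows is a different question. The two have the same answer only when control attendance is much the same across IMD or the intervention has no effect.

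The article states an inequality aim and defines a worthwhile effect in percentage points, but the scale stated for the gradient analysis of attendance is the odds ratio. A null interaction could then be taken to mean that all groups benefit equally, although the absolute gains differ. Conversely, equal absolute gains would appear as a larger odds ratio in the more deprived.

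**Working it through.** **Inputs from the article.** Control attendance 30%; difference sought 9 points (30% to 39%), or 10 points before the contamination allowance; 559 per group at 80% power and α = 0.025; 590 per group after 5% loss; 1:1 allocation.

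**Assumed.** Control rates by IMD, which the article does not give. I split the sample into a more and a less deprived half averaging 30% and vary the spread. Site effects are ignored, and the test is taken as two-sided.

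**The plan's own figure.** The usual two-proportion formula for 30% against 39% is n = [2.241·√(2·0.345·0.655) + 0.842·√(0.30·0.70 + 0.39·0.61)]² / 0.09². It gives 530 per group, or 552 with continuity correction; 31% against 40% with the correction gives exactly 559. Then 559/0.95 = 588.4, so 589 against the stated 590. The stated figure is reproduced closely enough to use its effect size.

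**Common odds ratio.** (0.39/0.61)/(0.30/0.70) = 1.492.

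**Rates under an exactly null interaction.** p₁ = OR·p₀ / (1 − p₀ + OR·p₀). For p₀ = 20%: 0.25 × 1.492 = 0.373, and 0.373/1.373 = 27.2%. For p₀ = 40%: 0.667 × 1.492 = 0.995, and 0.995/1.995 = 49.9%.

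| Assumed control rates (more / less deprived) | Intervention rates | Gains (points) | Gap before → after (points) | Ratio of rates before → after |
|---|---|---|---|---|
| 27% / 33% | 35.6% / 42.4% | 8.6 / 9.4 | 6.0 → 6.8 | 1.22 → 1.19 |
| 25% / 35% | 33.2% / 44.5% | 8.2 / 9.5 | 10.0 → 11.3 | 1.40 → 1.34 |
| 20% / 40% | 27.2% / 49.9% | 7.2 / 9.9 | 20.0 → 22.7 | 2.00 → 1.84 |
| 15% / 45% | 20.8% / 55.0% | 5.8 / 10.0 | 30.0 → 34.1 | 3.00 → 2.64 |

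Under a constant odds ratio the absolute gain rises with the control rate up to p₀ = 1/(1 + √OR) = 45%, well above the 30% average. That is why the gap widens in every row. Using 30% to 40% instead (OR 1.556), the gap goes to 11.4 points at 25/35% and 22.9 points at 20/40%. With no spread in control rates there is no widening.

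**The converse.** Equal 9-point gains at 20% and 40% give odds ratios of (0.29/0.71)/(0.20/0.80) = 1.63 and (0.49/0.51)/(0.40/0.60) = 1.44, a ratio of 1.13.

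**Precision.** With all 1180 participants in two equal halves there are 295 per cell.

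- *Absolute scale, 20/40%.* The standard error of the difference in risk differences is √[(0.20·0.80 + 0.272·0.728 + 0.40·0.60 + 0.499·0.501)/295] = 0.0536, so the 95% CI is about ±10.5 points. At 25/35% it is about ±10.7.
- *Odds-ratio scale, 20/40%.* The standard error of the log interaction is √Σ[1/(295·p(1 − p))] = 0.257. The 95% CI spans a factor of exp(1.96 × 0.257) = 1.65 either way, and 80% power needs a ratio of odds ratios of about exp(2.80 × 0.257) = 2.05.
- *Edge of non-significance.* If the less deprived half had the larger odds ratio by a factor of 1.65, split evenly around 1.492, the rates would be 22.5% and 56.1%: a 20-point gap becomes about 34 points. A non-significant interaction therefore excludes little.

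**The case against.** The strongest reply is that the planned test answers the stated objective. That objective asks whether effects differ across the gradient and names no scale, and a treatment-by-IMD interaction is a standard answer. This stands. A reader might infer that the analysis fails its objective or is the wrong model; the article does not support that.

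A reader might also infer that the trial could report success while widening a gap it was meant to narrow. That goes too far, for four reasons.

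- The inequality wording describes what the intervention was developed to do. It refers to health inequalities and sets no estimand or scale.
- The direction depends on the scale: the ratio of rates narrows in every row where the absolute gap widens.
- The background gradient is that of the general population. Eligibility {10} requires no planned visit for two years or more and no regular dentist, and selecting on non-attendance may flatten the gradient.
- Nothing in the article says that a null interaction will be reported as equal benefit.

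Two further replies stand. The widening is small against the precision available, about 1 to 3 points against ±10 to 11. And a full analysis plan exists but is not shown and may add absolute summaries, so it cannot be said that the odds ratio is all that will be reported.

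What survives is narrower. The scale stated for attendance is the odds ratio, the article measures a worthwhile effect in percentage points, and the two can point in different directions.

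The word for IMD in Table 1 might suggest that IMD will be analysed as a mediator. It will not: section {20b} uses it in an interaction, and the mediation analysis concerns psychological variables only.

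**Conclusion.** The point holds for attendance only, as an inexpensive improvement rather than an error. The logistic interaction is legitimate, but alone it does not show what happens to the absolute attendance gap. With the interaction exactly null and an odds ratio of 1.49, the gap widens by about 1.3 points at control rates of 25/35% and 2.7 points at 20/40%, while the relative gap narrows.

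These sizes rest on assumed control rates by IMD, a split into two equal halves, and no allowance for site. A flatter gradient shrinks them: 0.8 points at 27/33%, and zero with no gradient. The low power of the interaction is a separate reason not to read a non-significant result as equal benefit. OHIP-14 is modelled linearly, so its interaction is already on the absolute scale.

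**What to change.** - Keep the logistic model and its IMD-by-intervention interaction.
- From the same model, also report standardised attendance by arm and the risk difference at set IMD levels, for example quintile midpoints. Give the contrast in risk differences between the most and least deprived, with its 95% CI.
- State in advance that the gradient conclusion for attendance will be read on both scales, and that a non-significant interaction will not be taken as equal benefit.
- In Table 1, replace the word mediator for IMD with effect modifier. This is a wording correction only: IMD is derived from the postcode collected at baseline and no planned analysis treats it as a mediator.

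The cost is a few lines of analysis-plan text and one post-estimation step (delta method or bootstrap), with no new data. The drawback is an imprecise contrast, with a 95% CI of about ±10 to 11 points, which should be presented as descriptive. Making the absolute contrast the main gradient result would be a matter of preference and is not needed.
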